### Mixed quantitative and qualitative methods process evaluation

A mixed quantitative and qualitative methods process evaluation will be nested within the feasibility trial. The aims are (1) evaluate the feasibility and acceptability of trial procedures, and (2) to investigate the implementation (feasibility, fidelity and acceptability) of delivery of PST.

#### Participants

Trial participant women, research assistants, supervisors and intervention providers will be included in this mixed study design.

#### Sampling

Women who received the intervention will be purposively selected for semi-structured interview based on their status of completion of the intervention sessions (four sessions of PST). We estimate that about eight participants, both who did and did not complete the PST sessions, will be selected. However, the number of participants will depend on when no new information is obtained. All research assistants, supervisor and providers will be invited to participate in the FGDs. Two separate FGD sessions (one for providers and second for supervisors and research assistants) will be conducted.

#### Process evaluation outcomes

The nested process evaluation investigates two categories of feasibility/implementation outcomes: trial procedure feasibility and acceptability (see Table 2) and implementation of delivery of PST (Table 3). The primary outcome for feasibility trial procedures is dropout rate. Dropout will be defined as the number of women lost to follow up at either of the follow up assessments. Secondary outcomes related to trial procedures and data collection procedures are listed in Table 2. These include participant recruitment rate, feasibility and suitability of eligibility criteria, feasibility of data collection procedures (clarity of baseline questionnaires, characteristics of outcome measures such as missing data, time needed to complete the questionnaires and data collection), adequacy of masking and practical administrative challenges and acceptability of trial procedures (number of refusals to recruitment and screening; qualitative exploration of experience of trial procedures).

**Table 2 Tab2:** Outcomes of trial procedures

Feasibility outcomes	Data source	Feasibility success	Timing
Feasibility of recruitment			
• Dropouts from the trial/completion of sessions	screening logs, supervision minutes and session records	50% or more women complete sessions	Pre- and during intervention
▪ Feasibility and suitability of eligibility criteria restrictive/too inclusive	Administrative (screening logs) Proceedings of weekly supervision meeting (Agenda: suitability of eligibility)	# of women excluded due to each exclusion criteria	Pre-intervention
Feasibility of data collection procedures			
▪ Clarity of baseline questionnaires (layout, instructions, order of tools))	Proceedings of weekly supervision meeting (Agenda: clarity, time and acceptability of items	20 minutes to complete baseline and follow up battery	Pre-intervention
▪ Characteristics of outcome measures (SD of the outcome and missing data)	Outcome assessment tools	Less than 5% missing data	Post baseline assessment
▪ Time needed to complete questionnaires (reasonable or burden to participants)	Time recorded on questionnaire FGD with supervisors and research assistants	20 minutes to complete baseline and follow up battery	Pre-intervention
• adequacy of masking of assessors and time needed to collect and analyse the data	Administrative documents FGD with supervisors and research assistants		since start of recruitment
▪ Practical administrative and resource challenges to conduct the study (e.g. budget requirements, time, space, staff, skill, intervention materials)	In-depth interviews with participants and healthcare providers, FGD with supervisors and research assistants		Post/ During intervention
Acceptability of trial procedures			
▪ Obstacles to recruitment (recruitment rates, number of eligible patients, number of refusals and screenings)	Administrative data and qualitative data from healthcare providers and participants Proceedings of weekly supervision meeting (Agenda: recruitment challenges)	Less than 10% refusal to be randomized and screened in the flowchart	Pre-intervention
▪ Participant willingness to be randomized (# of women)	Administrative data (enrolment log)	Less than 10% refusal to be randomized	Post/during intervention

**Table 3 Tab3:** Implementation outcomes for delivery of PST

Implementation outcomes	Data source	Feasibility success	Timing
Feasibility of PST			
▪ Completion of PST activities (homework)	Clinical logs	Completion of homework (80%)	During intervention
▪ Practical administrative and resource challenges to conduct the study (e.g. budget requirements, time, space, staff, skill, intervention materials)	Semi-structured interviews with participants and healthcare providers, FGD with supervisors and research assistants		During intervention
▪ All adverse events, including both expected and unexpected (identification, documentation, referral and reporting)	Administrative data (notes in routine clinical data), participant self-report, identified if the woman drops out of the study.	5% or less report of Adverse Events	During intervention
Fidelity (adherence of therapist to contents, methods and ethical standards)	Audio rating using adherence/fidelity checklist, supervision records	More than 80% adherence	During intervention
Acceptability of intervention delivery			
• Participants’ satisfaction with therapeutic services	Helping alliance questionnaire (HAQ) [78]		After intervention
• Suitability of measures	Proceedings of weekly supervision meeting and FGD with research assistants		During intervention
▪ Provider and service user perception	In-depth interviews (participants and healthcare providers) [79]		After intervention
▪ Relevance of the intervention	In-depth interviews (participants and healthcare providers) [79], session records.		After intervention
▪ Retention and follow up rates, number and duration of sessions attended	Administrative data	50% or more women complete sessions	During intervention
Appropriateness and Sustainability of intervention	In-depth interviews (participants and healthcare providers) [79]		After intervention
Implementation costs	locally adapted Client Service Receipt Inventory (CSRI) [73]) and administrative data		During/post intervention
Implementation strategy (task-shared psychological intervention)	Therapist competence to deliver PST (ENACT scale [56, 57])	90% or more done well (3 points) on each item	

To document the successful implementation of an intervention, the following implementation outcomes are recommended: acceptability, adoption, appropriateness, feasibility, fidelity, implementation cost and sustainability [78] as detailed in Table 3.

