**Table 1 Tab1:**
[figure not shown]
Schedule of enrolment, interventions and assessments

The primary outcome for a future efficacy trial will be change in PHQ-9 score using the locally validated Amharic version of PHQ-9 [64], assessed at T0, T1 and T2. The PHQ-9 has been widely used as a clinical outcome measure of treatment for depression [65, 66]. In Ethiopia, PHQ-9 has been validated in antenatal women [67] and in primary care settings in the neighbouring district of the current study, with the optimal cut-off point indicating probable depression identified as five or more in primary care attendees [47]. At that cut-off, PHQ-9 had a sensitivity of 83.3% and specificity of 74.7% for detection of major depressive disorder. In previous studies, a 50% reduction in PHQ-9 depressive symptom scores [66] after 6–8 weeks was defined as treatment response. A 50% reduction of PHQ-9 score at nine weeks (T1) follow up will be defined as a treatment response for future efficacy trial.

Secondary outcomes to be collected at T0, T1 and T2 are disability (change in WHO disability Assessment Scale, WHODAS, score) [68], anxiety [Generalised Anxiety Disorder-7 scale; GAD-7) [69], PTSD symptoms checklist (PCL-5) [70, 71], intimate partner violence (non-graphic IPV test with five items [72] and WHO multi-country study questions [73]), number of emergency healthcare visits and costs (locally adapted Client Service Receipt Inventory (CSRI) [74]).

At T2, only (4 to 6 weeks postnatal) self-reported information on delivery setting, prolonged labour, sepsis, unsafe abortion, perinatal mortality (stillbirth and neonatal mortality), time of onset of breast-feeding and child health (maternal report of diarrhoea, fever and refusal to breast feed) will be collected.

Potential mediators will be assessed at T0, T1 and T2: attitudes towards gender roles (attitude towards gender roles scale [75]), mastery (Multicultural mastery scale [76]]), self-efficacy of coping with depression (adapted self-efficacy scale [76]) and perceived social support (Oslo Social Support Scale (OSS-3)), previously used in Ethiopia [77] (Table 1).

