At T0, a questionnaire will collect data about socio-economic and demographic characteristics of the participants (age, education, marital status, age at marriage, husband’s occupation and educational level, residence and pregnancy intention), obstetric history, including parity, pregnancy intention and gestational age, past psychiatric history and list of traumatic experiences. An item from Ethiopian Demographic Health Survey (EDHS (previously used in our study [7]) will be used to assess pregnancy intention.

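### The 20-minute limit in Table 2 names the follow-up battery but is timed before any follow-up, and it also serves as the only success criterion for questionnaire clarity

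*Protocol article*

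**What the plan says.** In the protocol article, Table 2 (under Process evaluation outcomes) has a block on the feasibility of data collection. Two of its rows matter here.

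- The clarity row, "Clarity of baseline questionnaires (layout, instructions, order of tools", draws on the proceedings of the weekly supervision meeting, with "Agenda: clarity, time and acceptability of items". Its success criterion is "20 minutes to complete baseline and follow up battery" and its timing is "Pre-intervention".
- The time row, "Time needed to complete questionnaires (reasonable or burden to participants", draws on "Time recorded on questionnaire" and a focus group with supervisors and research assistants. Its success criterion and timing are the same as those of the clarity row.

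The section on assessment of trial participant outcomes defines T0 as the pre-intervention baseline, T1 as 9 weeks after recruitment and T2 as 4–6 weeks after delivery. It lists a common set of outcome and mediator measures for all three points. Two modules belong to one point only: "At T0, a questionnaire will collect data about socio-economic and demographic characteristics of the participants", together with obstetric, psychiatric and trauma history; and "At T2, only (4 to 6 weeks postnatal) self-reported information on delivery setting, prolonged labour, sepsis", together with perinatal mortality, breast-feeding and child health.

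**The concern.** The time row contradicts itself: its criterion covers a battery that has not yet been given at the time the row is to be judged. In the clarity row the criterion does not match the outcome. A confusing question can be answered quickly, and a clear one can take longer because the interviewer explains it. The Discussion describes the setting as one of low literacy, so the second case is not remote.

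Clarity and completion time are both named secondary outcomes of the feasibility trial, whose first aim is to test procedures for a later efficacy trial. Applied as written, the two rows could support a conclusion about follow-up interviews drawn from baseline interviews, and a conclusion about clarity drawn from speed. Long follow-up interviews could plausibly also contribute to loss at follow-up, the primary outcome, but the protocol neither states nor quantifies that link.

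**Working it through.** There is no power or sample-size figure to reproduce. The check sets the timing column of Table 2 against the assessment schedule.

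**1. What falls in the stated window**

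| Assessment | When | Pre-intervention? | Planned interviews (maximum) |
|---|---|---|---|
| T0 | baseline | yes | 50 |
| T1 | 9 weeks after recruitment | no | 50 |
| T2 | 4–6 weeks after delivery | no | 50 |

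The PST intervention section places the four sessions within 8 weeks and before delivery, so T1 and T2 both follow it. One of three assessments lies inside the window. The two outside it are the ones meant by the follow-up battery: 50 × 2 = 100 planned interviews if nobody is lost.

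The timing entry is not a generic label. Nearby rows of Table 2 use other entries: after the baseline assessment, since the start of recruitment, and after or during the intervention. The Enhanced usual care section likewise separates one pre-intervention assessment from two follow-up assessments.

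**2. What T0 can say about T1 and T2**

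Write the interview times, from the content listed in the article, as:

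- T0 = common measures + history module
- T1 = common measures
- T2 = common measures + postnatal module

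T0 − T1 = history module, which is positive. At an equal pace, a T0 interview within 20 minutes implies a T1 interview within 20 minutes, so T0 is informative for T1 and errs on the cautious side. The converse fails: a T0 overrun may be due to the history module alone.

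T2 − T0 = postnatal module − history module. The article gives the length of neither, so the sign is unknown. T0 cannot settle T2 in either direction. The part of the follow-up with no counterpart at T0 is therefore the postnatal module, in at most 50 of the 100 follow-up interviews.

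**3. Whether the reading of the limit matters**

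The criterion does not say whether 20 minutes applies to each sitting or to baseline and follow-up together. The timing fails either way. Per sitting, the follow-up sittings have not happened; combined, the sum cannot be formed until they have.

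**4. The clarity row**

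The outcome is layout, instructions and order of tools. The data source is supervision proceedings with clarity on the agenda. The success criterion is a duration. The first two match and the third does not. Pre-intervention timing is right for this row, since it concerns baseline questionnaires.

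**The case against.** The best reply is that this is a mislabelled cell. The criterion itself mentions follow-up, the source is the time noted on the questionnaire with no restriction to baseline, and nothing suggests that follow-up interviews go untimed. That is a fair reading of intent, and the data would probably exist. It does not remove the conflict between the two cells, and a team applying the table literally would judge the row before T1.

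On clarity, the reply is that the limit does not stand alone. Weekly supervision discusses clarity, Table 3 has a row on the suitability of measures, and Table 2 asks for under 5% missing data on the outcome tools. All of this stands. A reader might infer that unclear items which are skipped simply pass. The documents do not support that, because the missing-data row would catch part of it. That row covers outcome tools only, however, and does not detect items answered without being understood. None of these sources sets a success criterion for clarity.

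A reader might also infer that 20 minutes is too short for so many instruments. That is a separate question. The instruments differ in length, and the article gives no completion times from which to judge it.

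Finally, these are descriptive secondary outcomes, and the article ties no rule for proceeding to the efficacy trial to them. That limits the weight of the point.

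**Conclusion.** The point holds in a limited form. In the time row, criterion and timing contradict each other: the follow-up part cannot be judged under the stated timing, and T0 can stand in for T1 but not for the postnatal module at T2. In the clarity row, the only success criterion measures something other than clarity.

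It would go too far to say that the trial cannot learn about follow-up burden or about clarity. Times are to be noted on the questionnaires and clarity is discussed in supervision; the fault lies in the stated success rules. The effect is confined to two named secondary outcomes. The definition of dropout and the efficacy measures are untouched. The correction is still worth making, because following the table as written could give a wrong feasibility conclusion on both outcomes.

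This rests on the content listed in the text, since the schedule in Table 1 is not visible. If a further instrument is given only at T1, T0 would be less informative for T1. One candidate is the Helping Alliance Questionnaire, which Table 3 places after the intervention.

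**What to change.** Two edits to Table 2.

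1. **Time row.** Change the timing to T0, T1 and T2. Compare the times noted on the questionnaire with the limit separately at each point, so that the postnatal module is judged where it is used.
2. **Clarity row.** Keep the pre-intervention timing. Replace the 20-minute limit with a criterion drawn from the supervision proceedings already named as the source, such as the share of items flagged as unclear or needing explanation.

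The cost is small because both data sources are already in the plan. The follow-up result will be available only after T2, and someone must tally flagged items from the supervision records. The article says only that time is noted on the questionnaire, so the team should confirm that the entry gives the duration of each interview.

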#### Sample size

Fifty participants (25 in the intervention and 25 in the enhanced usual care group) will be recruited for this feasibility trial. This sample size will enable us to detect a dropout rate of 7% with 95% confidence interval and a 5% margin of error [50]. A sample size of 24–50 is recommended for feasibility studies [51].

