#### PST intervention

PST is a commonly used psychotherapy [38, 52] that has comparable efficacy to other psychotherapies such as behavioural activation, cognitive behavioural therapy and social skills training and medication [53, 54]. The PST approach assumes that depressive symptoms are the negative consequences of maladaptive coping in response to problems [55]. The intervention applies principles of evidence-based problem-solving therapy [55] to improve a person’s problem solving and coping skills. In this approach, there are three phases. In the first phase, women are helped to identify the most important things in their life. In the second phase, they identify a list of problems that challenge attainment of important goals in their life and classify the problems into three categories: ‘Problems that are upsetting but not relevant to the most important things in one’s life’ (group A); ‘Problems that are important but, insoluble’ (group B); and ‘important and soluble problems’ (group C). Any psychological therapy should be adapted to the cultural setting to ensure effectiveness, acceptability and feasibility [56]. PST has been contextually adapted and manualised for pregnant women with antenatal depressive symptoms in rural Ethiopia ([name] 2020, unpublished). The adaptation was based on the Medical Research Council guidelines for developing and evaluating complex interventions [34] and the ADAP-ITT approach [35]. This comprised a series of theory of change workshops, adaptation workshops and in-depth interviews with women with a history of perinatal depression and healthcare providers, and discussions after role play (theatre test).

Participants randomised to the intervention arm will receive four individual sessions of locally adapted and manualised PST, along with enhanced usual care, at a time convenient to them in a private room of the PHC facility. Intervals between sessions will range from a minimum of 2 days to a maximum of 2 weeks over a period of 8 weeks ensuring that all sessions are completed during pregnancy. The first session will last for 1 h and the remaining sessions will last for approximately 40 min each.

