
Clinical records and consent forms will be kept in the research office for confidentiality. Research staff will use telephone contact to follow up participants who withdraw without reporting to the research office in order to check for unreported adverse events.

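### Table 3 sets an adverse event report rate of at most 5% as feasibility success in a row meant to show that events are found and reported, so better capture makes PST look less feasible

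*Protocol article*

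**What the plan says.** The mark is in Table 3 of the protocol article ("Implementation outcomes for delivery of PST"), under feasibility of PST. The outcome in that row is "All adverse events, including both expected and unexpected (identification, documentation, referral and reporting", closed by a bracket. The feasibility success column reads "5% or less report of Adverse Events", and the timing is during the intervention. The data source column reads "Administrative data (notes in routine clinical data), participant self-report, identified if the woman drops out of the study".

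Three other places bear on it:

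- Sample size: "Fifty participants (25 in the intervention and 25 in the enhanced usual care group) will be recruited for this feasibility trial".
- PST intervention, on the window: sessions run "over a period of 8 weeks ensuring that all sessions are completed during pregnancy".
- PST intervention, on extra capture: research staff telephone women who withdraw without telling the research office, "in order to check for unreported adverse events".

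The row does not say whether the 5% refers to women or to events, or which women form the denominator. Nothing in the article narrows the mark to serious events or to events related to PST.

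**The concern.** The outcome and its success mark pull in opposite directions. The row asks whether adverse events are found, written down, referred and reported. Success is then a low number of reports. A team that asks carefully will record more events and move towards failing; a team that asks little will move towards passing.

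The mark also counts everything. Women are observed for up to eight weeks of pregnancy, and some will have events that have nothing to do with a talking therapy. With no relatedness criterion and no comparison with the enhanced usual care arm, a figure above 5% cannot be read as harm from PST, and a figure below 5% cannot be read as safety. The trial exists to inform the design of an efficacy trial, so a misleading safety benchmark is worth removing now.

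**Working it through.** **Inputs.** The threshold of 5% is from Table 3. The arm size of 25 and the total of 50 are from the Sample size section. That the 25 PST women are the denominator is an inference from the table's subject, so 50 is run as well. The true risk that a woman has any adverse event in the window is not given; it is assumed over a range. Women are taken as the unit, and as independent.

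**The plan's own figure.** The article gives no derivation for the 5%, so there is nothing to reproduce. It can only be turned into a count.

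**Step 1: the allowed count.**

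- 25 women: 0.05 × 25 = 1.25, so at most 1 (1/25 = 4%); 2/25 = 8% fails.
- 50 women: 0.05 × 50 = 2.5, so at most 2 (2/50 = 4%); 3/50 = 6% fails.

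**Step 2: chance of meeting the mark with full capture.** For 25 women, P(pass) = (1 − p)^25 + 25p(1 − p)^24. At p = 0.05 this is 0.277 + 0.365 = 0.642. For 50 women it is the binomial probability of 2 or fewer.

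| Assumed true any-event risk | P(pass), 25 women | P(pass), 50 women |
|---|---|---|
| 1% | 97% | 99% |
| 2% | 91% | 92% |
| 5% | 64% | 54% |
| 10% | 27% | 11% |
| 20% | 2.7% | 0.1% |

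With 25 women, passing and failing are equally likely at a true risk of about 6.6%. The chance of passing falls to 5% at about 17.6%.

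**Step 3: effect of incomplete capture.** If a fraction c of affected women is captured, the observed risk is p × c. Take p = 20% and 25 women:

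- c = 100%: observed 20%, P(pass) 2.7%
- c = 50%: observed 10%, P(pass) 27%
- c = 25%: observed 5%, P(pass) 64%
- c = 10%: observed 2%, P(pass) 91%

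The true risk is the same in every line; only the quality of capture changes.

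**Step 4: what a pass or a fail tells us.** The exact (Clopper–Pearson) 95% interval is 0.1% to 20.4% for 1/25, a pass, and 1.0% to 26.0% for 2/25, a fail. The two intervals overlap almost entirely.

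**The case against.** The strongest reply is that this is one descriptive benchmark among many. The primary feasibility outcome is dropout, the analysis is descriptive, and no stop-or-go decision is tied to this row. Any percentage cut-off is imprecise with 25 women, so failing 36% of the time at a true 5% is not peculiar to this row. All of that stands, and it limits the consequences. It does not answer the point about direction: this mark improves as the activity it is meant to assess gets worse.

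A reader might go further and infer that the criterion must either fail on ordinary pregnancy events or pass through under-reporting. The document does not support that. It gives no background rate, and at a true risk of 1% or 2% the mark is met legitimately 97% or 91% of the time. The exclusion of acute illness and comorbid conditions lowers the background risk by an unknown amount.

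Nor do the postnatal outcomes show that background events are common in the window. The "self-reported information on delivery setting, prolonged labour, sepsis, unsafe abortion, perinatal mortality" items are collected only at 4–6 weeks postnatal, whereas the mark applies during an intervention completed in pregnancy, so most of them fall outside it. The number of emergency healthcare visits is also collected at nine weeks, but the article does not say whether these visits count as adverse events.

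It is also fair to say that definitions, seriousness grading and the counting unit are commonly left to a full protocol, and that nothing says events go unrecorded under enhanced usual care. Those gaps are not the point here; the stated mark is. The telephone check is a real safeguard, but it covers only women who withdraw silently.

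**Conclusion.** The concern holds as a fault in a stated success criterion. As written, the mark counts every adverse event, allows one woman in 25 (or two in 50) to report one, and becomes easier to meet as capture gets worse. It cannot separate harm from PST from background events in pregnancy. This does not depend on which denominator is used.

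The size is conditional. Failure is more likely than not once the captured any-event risk exceeds about 6.6% with 25 women; well below that, the mark would usually be met. Which case applies cannot be settled from the document. It would be too strong to say that a wrong decision on the efficacy trial follows, because the article ties no such decision to this row.

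**What to change.** Remove the 5% mark as a feasibility success criterion in Table 3. Replace it with a process target that matches the row's stated purpose, for example that all identified events are documented, referred where indicated and reported.

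Report the number and proportion of women with any, serious and related adverse events descriptively by arm, with exact intervals. Ask the same questions in both arms at the existing assessments, so that the additional PST sessions do not by themselves produce more reports in one arm.

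A numerical limit on related serious events should not carry the fix. With 25 women, even zero such events leaves an exact 95% upper limit of 1 − 0.025^(1/25) = 13.7%, so it would discriminate little. Whether to set one is for the safety lead, and none is proposed here.

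The cost is a change of table wording, a short common set of questions and a relatedness judgement; no extra visits are needed. The downsides are small: relatedness involves judgement, and the row no longer yields a single pass/fail rate.
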